**Fig. 1 Fig1:**
[figure not shown]
Study schema illustrating our specific aims, projected infant enrollment, and methodologic approach. Our prospective, observational cohort investigation will determine the associations of prolonged irradiation time (pIST) and metabolic changes of transfused RBCs to alterations in mesenteric oxygenation that may increase the risk for NEC in preterm infants weighing ≤1250 g. In addition, we will explore the implications of severe anemia (hemoglobin ≤8 g/dL) when infants are most vulnerable to NEC development, approximately 29–34 weeks’ gestation. Abbreviations: NIRS, near-infrared spectroscopy, RBC, red blood cell; PMA, post menstrual age; NEC, necrotizing enterocolitis; mesSO_2_, mesenteric regional oxygen saturation

##### Study design

We will prospectively investigate, using an established birth cohort design [18, 46], the associations between RBC transfusion (including characteristics of transfused RBCs), anemia, intestinal oxygenation, and NEC. We specifically aim to understand the relationship between pIST, donor RBC metabolomics profiles, and recipient anemia on MES-rSO_2_, as measured by NIRS, and the development of NEC (Fig. 1). Although many studies have characterized the association between NEC and transfusion, none have focused on improving our understanding of the underlying pathophysiology, particularly the intestinal oxygenation changes preceding NEC. Further, the safety and efficacy of various blood banking practices including the preparation of storage-aged RBCs (saRBCs) and repeat donor exposure in recipients remains unclear. The safe threshold of saRBC+/− pIST in infants is not known and longer-stored saRBCs, either before or after irradiation, may potentiate the RBC storage lesion. This study may provide new knowledge regarding the potential benefit or harm of various blood banking practices and may identify new potential mediators of NEC.

The study schema (Fig. 1) illustrates how we aim to characterize the association between metabolic changes in transfused RBCs relative to pIST, and adverse effects in the recipient through two approaches: in vivo NIRS trend monitoring of intestinal oxygenation, and in vitro RBC functional studies. The schema explains how variables will be compared to evaluate primary and secondary endpoints for each specific aim. Our primary endpoint is changes in MES-rSO_2_ trends in response to transfusion of saRBC+/− pIST as measured by NIRS (Aim 1). Secondary endpoints are 1) to determine the hazard ratio of NEC comparing infants transfused with saRBCs with and without pIST; (2) examination of metabolomics fingerprints of transfused RBC (in vitro) among infants with and without NEC (Aim 2); and 3) impact of severity of anemia over time during the NEC window (29–34 weeks postmenstrual age) on MES-rSO_2_ (Aim 3).

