## Methods

All RBC transfusions given to infants during hospitalization will be studied. All RBC transfused units are stored in citrate-phosphate-dextrose-adenine (CPDA-1) preservative solution. pIST and storage days will be recorded for each RBC transfusion. All infants will be monitored with NIRS prior to, during and up to 48 h following each transfusion. Consistent with epidemiologic reports of transfusion-related NEC and prior studies at the 3 centers, we anticipate approximately 20 (10%) infants will develop NEC while on study. For our 2:1 case-controlled metabolomic analysis, we will prospectively analyze 40 infants who do not develop NEC and compare to 20 infants with NEC. Within this sub-cohort, we will compare alterations in metabolic pathways from saRBC unit (in vitro) and infant blood sample (in vivo). We will then examine a third sub-cohort of 120 infants without NEC within the NEC “window” (29–34 postmenstrual weeks’). These infants will also be monitored weekly for 24–48 h with mesenteric NIRS to evaluate the relationship between anemic (hemoglobin < 8 g/dL) and non-anemic infants. Reports suggest that this specific population of infants are more likely to experience paradoxical reductions in MES-rSO_2_ substantially increasing the risk for NEC when transfusions are given [10, 36]. Analysis will also include assessment of hemoglobin as a continuous variable.

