### Statistical methods

We will use a novel statistical approach [51] implemented by the *NIRStat* R package for analyzing the NIRS data. Specifically, the *NIRStat* method models the observed MES-rSO_2_ time series with a nonparametric smooth function via penalized regression splines [49, 50]. It then provides accurate and robust statistical measures for characterizing the important features in rSO_2_ series. We will use the mean area under the fitted spline curves (MAUC) measure generated from the *NIRStat* package to measure the MES-rSO_2_ levels at baseline and then at post-transfusion. The MAUC changes from baseline to post-transfusion will be used to quantify the changes in MES-rSO_2_ due to transfusion. Two sample t-tests will be used to compare the changes in MAUC between saRBCs +/− pIST. Multivariate linear regression models will also be applied to model the changes in AUC in terms of pIST status (with pIST and without pIST) and other potential confounding factors. The multivariate analysis will allow us to assess whether the changes in MES-rSO_2_ differs significantly between saRBCs with pIST and those without pIST, controlling for other confounding factors.

The incidence of NEC and death will be estimated by the cumulative incidence function appropriate for competing risks. Gray’s method (modified log-rank test) will be used to compare NEC cumulative incidence according to baseline clinical characteristics. Cause-specific hazard ratios will be calculated to measure the degree of association between baseline characteristics and NEC, and between baseline characteristics and death by fitting a stratified Cox proportional-hazards regression model for competing risks. The competing risks model will be implemented using SAS PHREG using robust sandwich covariance matrix estimates to account for within-mother correlation that may occur in outcomes of multiple-birth infants.

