To guard against model overfitting, we will employ both clinical and statistical criteria in making decisions about which independent variables to include; and we will limit the number of candidate variables. In general, the results of models having fewer than 10 outcome events per independent variable are thought to have questionable accuracy and the tests of statistical significance may be invalid. The use of “machine-learning” covariate selection methods, such as bootstrap bagging, will be utilized to improve the reliability of identifying risk factors for NEC and death. The hazard ratio and its 95% confidence interval (CI) will be calculated for each factor in the presence of others in the final model for NEC and mortality.

For metabolomics analysis, we will examine associations between metabolic features of transfused RBC units and pre-transfusion pIST, alterations in MES-rSO_2_, and the development of NEC using an approach previously described [25]. Correlative analyses without pre-selecting specific metabolic pathways will be performed. Methods of analysis will include a number of gene set analysis, such as MSEA and MetaboAnalyst. We can also borrow from the gene expression packages to conduct more complex analysis of metabolite-set differential expression analysis as well as metabolite-set differential coordination analyses. The pathway level analysis will be followed by the detection of metabolites that contribute the most to the changes of metabolic pattern using the built-in scoring system of the packages.

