## Discussion

There is an urgent need for a large, hypothesis-driven, prospective study to examine the effect of both RBC unit and recipient factors on the physiologic perturbations that cause NEC [11]. Given that 75–90% of low birth weight infants receive one or more RBC transfusions [52, 53], it is reasonable to predict that NEC may result from a combination of pre-existing anemia and reduced intestinal oxygenation exacerbated by metabolic/functional changes in transfused RBCs, due to irradiation and pIST. This investigation may allow us to identify new modifiable factors that can be used to test targeted prevention strategies and mitigate this devastating disease.

We propose to investigate intestinal oxygenation changes that precede the development of NEC. Our overarching hypothesis is that irradiation of RBC units followed by longer storage times perturbs donor RBC metabolism and function, and these derangements are associated with paradoxical microvascular vasoconstriction, intestinal tissue hypoxia and injury and/or NEC in transfused premature infants with already impaired intestinal oxygenation due to significant anemia. Specifically, our primary goal is to characterize the association between metabolic changes in transfused RBCs relative to pIST, and adverse effects in the recipient by in vivo NIRS trend monitoring of intestinal oxygenation, and in vitro RBC functional studies. Our primary endpoint is changes in MES-rSO_2_ trends in response to transfusion of saRBC+/-pIST as measured by NIRS. The secondary endpoints are to determine the hazard ratio of NEC for low birth weight infants transfused with saRBCs +/-pIST, examine metabolomic fingerprints of transfused RBC in vitro, and examine the impact of anemia severity on MES-rSO_2_ trends.

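### The NEC hazard ratio compares infants with and without pIST, but pIST belongs to each transfused unit; an ever/never grouping would tie exposure to transfusion count and confound the result

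*Protocol article*

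**What the plan says.** All references are to the protocol article.

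- **Study design** gives the first secondary endpoint: "to determine the hazard ratio of NEC comparing infants transfused with saRBCs with and without pIST". The **Discussion** repeats it as "the hazard ratio of NEC for low birth weight infants transfused with saRBCs +/-pIST". Both compare infants.
- **Methods** records the exposure by transfusion: "pIST and storage days will be recorded for each RBC transfusion". It covers the whole stay: "All RBC transfusions given to infants during hospitalization will be studied". An infant may therefore contribute several units, some with and some without pIST. No rule is given for assigning that infant to a group.
- **Statistical methods** describes the competing-risks Cox model in these terms: "Cause-specific hazard ratios will be calculated to measure the degree of association between baseline characteristics and NEC". pIST is not named there. The model that does name it is the linear regression for the oxygenation endpoint, which will "model the changes in AUC in terms of pIST status (with pIST and without pIST) and other potential confounding factors".
- On the amount of information, Methods says "we anticipate approximately 20 (10%) infants will develop NEC while on study", and Statistical methods cautions that "models having fewer than 10 outcome events per independent variable are thought to have questionable accuracy".

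**The concern.** An exposure that varies from unit to unit is turned into a fixed label for the infant. If the label means having ever received a pIST unit, an infant stays in the comparison group only when every unit received was without pIST. That is likely after one transfusion and unlikely after several, so the pIST group would collect the heavily transfused infants.

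The article itself gives reasons to expect those infants to differ in NEC risk. The Background says that most premature infants are transfused for anemia of prematurity. It also cites the group's own cohort, in which severe anemia carried an adjusted cause-specific hazard ratio for NEC of 5.99 (95% CI 2.00 to 18.0).

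A hazard ratio away from 1 could then reflect how many transfusions an infant needed rather than how long the units were stored after irradiation. Study design says that the results may inform blood banking practice, so the difference matters.

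**Working it through.** **The plan's own figures.** No power or event calculation is given for the NEC hazard ratio. The figures in Table 1 concern the oxygenation endpoint and they reproduce: 55 per group, difference 10, SD 18 and two-sided alpha 0.05 (assumed) give 0.823 against the stated 0.82. They neither support nor weaken this point.

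**Step 1. Link between grouping and count.** Let p be the share of units with pIST and k the number of transfusions. The article gives neither, so both are assumptions. With units independent, P(ever pIST) = 1-(1-p)^k:

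| p | k=1 | k=2 | k=3 | k=4 | k=5 |
|---|---|---|---|---|---|
| 0.10 | 10% | 19% | 27% | 34% | 41% |
| 0.25 | 25% | 44% | 58% | 68% | 76% |
| 0.50 | 50% | 75% | 88% | 94% | 97% |
| 0.75 | 75% | 94% | 98% | 99.6% | 99.9% |

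The probability rises with k for every p strictly between 0 and 1.

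**Step 2. Size with no pIST effect.** Assume counts of 1, 2, 3, 4 and 6 in 30, 25, 20, 15 and 10% of transfused infants. Let NEC risk be proportional to m^(k-1), scaled to a mean of 10%, where m is the risk multiplier per extra transfusion for reasons other than pIST.

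Worked case, p = 0.5 and m = 1.3:
- Risks by count are 6.0, 7.8, 10.2, 13.2 and 22.3%.
- Never-pIST share: 0.30×0.5 + 0.25×0.25 + 0.20×0.125 + 0.15×0.0625 + 0.10×0.0156 = 0.248.
- Never-pIST infants have on average 1.60 transfusions and ever-pIST infants 2.93.
- NEC risk is 7.3% in never-pIST and 10.9% in ever-pIST infants, a ratio of 1.50.

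All risk ratios, ever against never:

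| p | m=1.0 | m=1.15 | m=1.3 | m=1.5 |
|---|---|---|---|---|
| 0.25 | 1.00 | 1.18 | 1.39 | 1.70 |
| 0.50 | 1.00 | 1.22 | 1.50 | 1.97 |
| 0.75 | 1.00 | 1.26 | 1.60 | 2.21 |

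These are closed-cohort risk ratios, not hazard ratios.

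**Step 3. Adding time.** A null simulation used a latent severity that drives both transfusion rate and NEC hazard (mean 3 transfusions over 90 days, 10% NEC, p from 0.10 to 0.75).
- Transfusions over the whole stay counted: NEC rate ratio 1.29 to 2.04 when severity raises NEC risk, and 0.99 to 1.05 when it does not.
- Only transfusions before NEC counted, but the label applied from time zero: 0.70 to 0.97 when severity raises NEC risk, and 0.57 to 0.70 when it does not. Infants who stay free of NEC for longer have more chances to receive a pIST unit, and this immortal time pulls the ratio down.

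**Step 4. Is time-updating enough?** In further null simulations (about 3 transfusions and 10% NEC over 70 days, p from 0.25 to 0.75), a correctly time-updated ever-pIST indicator gave hazard ratios of 1.16 to 1.20 with a log-severity SD of 0.5, and 1.46 to 1.55 with an SD of 0.8. A separate set of runs gave about 1.1 to 1.7. In that separate set, using the pIST of the most recent unit gave about 0.96 to 1.05, with or without strata for count.

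**Step 5. Information available.** With 20 events and a 1:1 split, the hazard ratio detectable with 80% power is exp((1.960+0.842)/√(20×0.25)) = exp(2.802/2.236) = 3.5. The article's own guard allows 20/10 = 2 variables. The 20 cases are counted over all enrolled infants, so those occurring after a first transfusion may be fewer. With 10 events the detectable hazard ratio would be 5.9.

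**The case against.** The strongest reply is that the ever/never rule is nowhere in the article. First transfusion, average pIST, or the transfusion before NEC would also fit the endpoint's wording. Under independent units, classification by the first or latest unit has no link to count. The sample size section, for the oxygenation comparison, expects infants to divide equally by pIST. An ever/never rule puts 75% of infants in the pIST group at p = 0.5 and 91% at p = 0.75, so an equal split fits only the low end (48% at p = 0.25). A condensed article may also leave the rule to a fuller document. **This stands in part.** A reader might infer that the plan commits to ever/never, and it does not. But it does fix an infant-level contrast for a unit-level exposure, and the analysis it describes for NEC does not deliver that contrast.

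Second, a reader might infer that the NEC model is restricted to baseline covariates. **That is too strong.** Statistical methods leaves the choice of variables to clinical and statistical criteria, reports each factor in the presence of the others, and mentions a stratified model without naming the strata. The fair statement is that the model is described only for baseline characteristics, and that neither pIST nor transfusion count is named for it.

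Third, size and direction are assumed. The Background reports conflicting evidence on transfusion and NEC, including no association in the group's own cohort, and with no gradient the ratio is 1.0. **This stands**, although anemia remains a route that the article itself supports.

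Fourth, stratifying by count is close to redundant once the most recent unit defines exposure, and thin strata cost information. **This stands too**, and it makes stratification a sensitivity analysis rather than the main one.

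**Conclusion.** The concern holds in a limited form. The first secondary endpoint compares infants on an exposure recorded per transfusion, and no stated analysis gives a hazard ratio free of a link to transfusion count. Under the natural but unwritten ever/never reading, membership of the pIST group rises with count for any mix of units. That result needs only independent units and a constant pIST share.

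The bias in the hazard ratio needs more: count must track NEC risk for reasons other than pIST. With assumed gradients of 15 to 50% per extra transfusion and pIST shares of 25 to 75%, the null risk ratio is about 1.2 to 2.2; with no gradient it is 1.0. A reader might infer that the bias must favor the study hypothesis. The documents do not support that, because fixing exposure from time zero can bring the ratio below 1. With about 20 events, distortion of this size could not be told apart from a real effect. This is worth correcting, but it concerns a secondary endpoint with no stated power and leaves the primary oxygenation endpoint untouched.

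**What to change.** In Study design (first secondary endpoint), Statistical methods (Cox model) and the Discussion (restated endpoint):

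1. Define the exposure in the NEC model as the pIST of the infant's most recent transfusion, time-updated, with time at risk starting at the first transfusion. This removes the built-in link to count and the immortal time.
2. As a sensitivity analysis, stratify that model by number of transfusions received so far (1, 2, 3 or more). Stratification adds no coefficient, so it does not use up the two-variable allowance. It also guards against the case where pIST is itself related to the order of transfusions.
3. Label the hazard ratio exploratory, given about 20 expected NEC events.

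The cost is a change of wording and a counting-process data set built from records already planned for each transfusion. There are two downsides. The estimand becomes recent rather than cumulative exposure, and the stratified analysis loses some information where risk sets are small. Confounding by illness that is unrelated to count would still need the covariate selection already planned.

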##### Study population and eligibility criteria

Our Emory University Institutional Board Review approved study we will enroll subjects at three sites in metro-Atlanta, Georgia. All infants with birthweight ≤1250 g in any of the 3 participating neonatal intensive care will be eligible for enrollment. Infants to be excluded are those who are not expected to live beyond 7 days of life (based on assessment of attending neonatologist), presence of a severe congenital anomaly, RBC or platelet transfusion received at an outside facility or prior to study screening, or maternal refusal to participate. Written informed consent from a parent or guardian will be obtained by a study investigator for each patient before enrollment. Infants will be screened for eligibility, and enrolled within 7 days of birth.

##### Sample size estimation

We aim to enroll a total of 220 infants into the study. We assume 110 of these infants (50%) will receive RBC transfusion and undergo NIRS monitoring. Analysis comparing two groups, divided equally among infants by pIST, would provide more than 80% power to detect a difference of 10% in pre- and post-transfusion mean area under the curve MES-rSO_2_ change (standard deviation = 18) between groups or 90% power to detect a difference as small as 6% in MES-rSO_2_ with a standard deviation of 9 (Fig. 1 and Table 1). However, the number of infants enrolled in the study that receive a transfusion and have NIRS monitoring may be lower than 110. Therefore, we have provided power estimates for analysis of a sample size of 72 infants with RBC transfusion and NIRS monitoring (33% of the enrolled cohort). This will generate 80% power to detect a difference of 12% in pre- and post-transfusion mean area under the curve MES-rSO_2_ change between the two groups if the final sample size is 72 infants (36 per group) and the estimated standard deviation for MES-rSO_2_ change is 18. A secondary analysis evaluating pIST a continuous variable will also be performed, which will likely yield greater power for each of the scenarios presented.

**Table 1 Tab1:** Sample Size and Power Estimates

Groups	*n* = 220 transfused				*n* = 110 transfused				*n* = 72 transfused			
	SD = 9		SD = 18		SD = 9		SD = 18		SD = 9		SD = 18	
Difference in MES-rSO_2_ AUC change (%)	Effect Size	Power	Effect Size	Power	Effect Size	Power	Effect Size	Power	Effect Size	Power	Effect Size	Power
6	0.67	1	0.33	0.69	0.67	0.93	0.33	0.41				
8	0.89	1	0.44	0.91	0.89	1	0.44	0.64				
10	1.11	1	0.56	0.98	1.11	1	0.56	0.82	1.11	1	0.56	0.64
12	1.33	1	0.67	1	1.33	1	0.67	0.93	1.33	1	0.67	0.8

Abbreviations: *MES-rSO*_*2*_ mesenteric regional oxygen saturation, *AUC* area under curve, *SD* standard deviation

## Methods

All RBC transfusions given to infants during hospitalization will be studied. All RBC transfused units are stored in citrate-phosphate-dextrose-adenine (CPDA-1) preservative solution. pIST and storage days will be recorded for each RBC transfusion. All infants will be monitored with NIRS prior to, during and up to 48 h following each transfusion. Consistent with epidemiologic reports of transfusion-related NEC and prior studies at the 3 centers, we anticipate approximately 20 (10%) infants will develop NEC while on study. For our 2:1 case-controlled metabolomic analysis, we will prospectively analyze 40 infants who do not develop NEC and compare to 20 infants with NEC. Within this sub-cohort, we will compare alterations in metabolic pathways from saRBC unit (in vitro) and infant blood sample (in vivo). We will then examine a third sub-cohort of 120 infants without NEC within the NEC “window” (29–34 postmenstrual weeks’). These infants will also be monitored weekly for 24–48 h with mesenteric NIRS to evaluate the relationship between anemic (hemoglobin < 8 g/dL) and non-anemic infants. Reports suggest that this specific population of infants are more likely to experience paradoxical reductions in MES-rSO_2_ substantially increasing the risk for NEC when transfusions are given [10, 36]. Analysis will also include assessment of hemoglobin as a continuous variable.

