#### Severity of Anemia and oxygen delivery to intestines

Severe anemia, leading to decreased oxygen delivery, may cause intestinal injury that predisposes an infant to NEC. Alkalay and colleagues [36] demonstrated that infants who appeared clinically “stable” with either significant anemia (hematocrit < 21%) or milder anemia (hematocrit 22–26%) had high cardiac output and restricted intestinal blood flow. Singh calculated that each percent decrease in nadir hematocrit led to a 10% increase in odds for NEC (OR 1.10; 95% CI: 1.02–1.18; *P* = 0.01) [10]. In our retrospective study, infants who developed NEC after transfusion had lower hematocrits 1 week prior than those without NEC [8]. We also found lower mesenteric oxygen saturation (MES-rSO_2_) measured by NIRS during and after transfusions in infants who developed NEC, and enteral feedings given during RBC transfusion worsened this effect [9]. Furthermore, a recent prospective study from our group found the rate of NEC was significantly increased among VLBW infants with severe anemia (≤ 8 g/dL) in a given week compared with those who did not have severe anemia (adjusted cause-specific hazard ratio, 5.99 [95% CI, 2.00–18.0]; *p* = .001) [18]. However, no study to date has prospectively compared longitudinal hemoglobin/hematocrit measures, MES-rSO_2_, and development of NEC in this population.

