##### Aims

The aims of this prospective, observational study are to (Fig. 1): 1) Determine the associations between RBC storage after irradiation (pIST), metabolic alterations in stored/irradiated RBCs, and changes in mesenteric digestive tract regional saturation of oxygen (MES-rSO_2_) measured by NIRS; 2) Compare in vitro measures of RBC function, and metabolic changes, between RBC products transfused to infants who develop NEC compared to matched control infants who do not; and 3) Explore the clinical implications of severe anemia (hemoglobin ≤8 g/dL) during the vulnerable “NEC window period” of 29–34 weeks postmenstrual age in the responses of infants < 1250 g to RBC transfusion. Our overarching hypothesis is that irradiation of RBC units followed by longer storage perturbs RBC metabolism and function leading to paradoxical microvascular constriction, mesenteric tissue hypoxia, and increased risk for NEC in transfused premature infants with already impaired intestinal oxygenation secondary to significant anemia.

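### Aim 3 compares MES-rSO2 in anemic and non-anemic infants only among infants without NEC, a later event that the protocol ties to both, so the difference is biased toward zero

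*Protocol article*

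**What the plan says.** All places are in the protocol article.

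- **Analysis set (Methods).** "We will then examine a third sub-cohort of 120 infants without NEC within the NEC" window of 29–34 postmenstrual weeks. These infants have mesenteric NIRS for 24–48 h each week "to evaluate the relationship between anemic (hemoglobin < 8 g/dL) and non-anemic infants". Hemoglobin will also be analysed as a continuous variable.
- **Endpoint (Study design).** The third secondary endpoint is the "impact of severity of anemia over time during the NEC window" on MES-rSO2.
- **Purpose (Aims).** "Explore the clinical implications of severe anemia (hemoglobin ≤8 g/dL) during the vulnerable" NEC window.
- **Anemia and NEC (Background, section on severity of anemia).** The group's earlier cohort found an "adjusted cause-specific hazard ratio, 5.99" (95% CI 2.00–18.0) for NEC with severe anemia in a given week.
- **MES-rSO2 and NEC.** The same section reports lower MES-rSO2 during and after transfusion in infants who developed NEC. Methods justifies the sub-cohort in the same terms: "Reports suggest that this specific population of infants are more likely to experience paradoxical reductions in" MES-rSO2, which it says substantially raise NEC risk when transfusions are given.

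No section gives a reason for leaving NEC infants out of Aim 3, and none says that infants who later develop NEC keep their earlier recordings in the analysis.

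**The concern.** Whether an infant develops NEC is not known when the weekly recordings are made. A set defined as infants without NEC is therefore defined by a later event. The protocol's causal account has severe anemia raising NEC risk and low MES-rSO2 raising NEC risk. NEC is then a common consequence of the exposure and the endpoint being compared.

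Excluding NEC cases has two effects. It removes a larger share of anemic than of non-anemic infants, and among the anemic it removes mainly those with the lowest saturations. The anemic infants who remain look better oxygenated than the anemic group really was, and the contrast moves toward no difference. A small or null Aim 3 result could then be read as showing that severe anemia does little to intestinal oxygenation, when part of that result would come from how the set was chosen.

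**Working it through.** **The plan's own figure.** Methods expects approximately 20 infants (10%) with NEC, and Sample size estimation states: "We aim to enroll a total of 220 infants into the study". 0.10 × 220 = 22, and 20/220 = 9.1%, so the figures agree up to rounding. About 220 − 20 = 200 infants stay NEC-free, of whom 120 would be 60%.

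**Step 1: how unequal is the removal?** Inputs: 20 cases, 220 infants, a risk ratio of 6 (the hazard ratio of 5.99, rounded) and an assumed anemic share p, which the article does not give. The share of cases that are anemic is 6p / (6p + 1 − p).

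| p | anemic share of cases | anemic infants removed | other infants removed |
|---|---|---|---|
| 10% | 0.40 | 8/22 = 36% | 12/198 = 6% |
| 20% | 0.60 | 12/44 = 27% | 8/176 = 5% |
| 30% | 0.72 | 14.4/66 = 22% | 5.6/154 = 4% |

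This treats a weekly hazard ratio as a per-infant risk ratio and puts all 20 cases in the excluded set, so it is only indicative.

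**Step 2: how far does the difference shrink?** Assumed model, with A = 1 for anemic infants: MES-rSO2 (Y, centred on the non-anemic mean) is normal with mean −10·A and SD 18, and

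logit P(NEC) = a + g·A − b·(Y/18), with b = ln 1.5, ln 2 or ln 3.

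The anemic share is 20%, and a is set so that overall NEC is 9.1%. The mean among infants kept is E[Y(1 − P)] / E[1 − P] within each group, found by numerical integration. Two cases for g:

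- *Only through MES-rSO2:* g = 0.
- *Also directly:* g set so that anemic infants have six times the NEC risk of the others (27.3% against 4.5%).

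| NEC odds per SD lower MES-rSO2 | g = 0: mean kept, non-anemic / anemic | difference | six-fold risk: mean kept, non-anemic / anemic | difference |
|---|---|---|---|---|
| 1 (no effect) | 0 / −10 | 10.0 | 0 / −10 | 10.0 |
| 1.5 | 0.63 / −9.24 | 9.9 | 0.33 / −8.07 | 8.4 |
| 2 | 1.01 / −8.61 | 9.6 | 0.55 / −6.88 | 7.4 |
| 3 | 1.44 / −7.74 | 9.2 | 0.84 / −5.55 | 6.4 |

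The loss is about 1–8% in the first case and 16–36% in the second. Simulating instead of integrating can move these values by about 0.1.

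**Step 3: one power illustration.** With 25% anemic, 10% NEC, a direct odds ratio of 5.99 and 2 per SD, the difference kept is 7.5 instead of 10. Without selection, 120 infants split 30/90, so (10/18)·√(30·90/120) = 2.64 and power is about 0.75 (two-sided 5% assumed). Among NEC-free infants the anemic share falls to about 20%, giving about 24/96 and (7.5/18)·√(24·96/120) = 1.83, so power is about 0.45.

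**The case against.** The strongest objection is about the reading. Infants cannot be picked for weekly monitoring on a status that is not yet known, so the phrase may mean NEC-free at each recording. For its Aim 2 controls the same paragraph refers to infants who do not develop NEC, and the change of wording could signal a change of meaning. The sentence about raised NEC risk also suits a group still at risk. On that reading, infants who later develop NEC contribute their earlier weeks and most of the problem goes. This is possible, but the text does not say it. Study design uses with and without NEC for the Aim 2 case and control groups, where it plainly means ever or never, so the same words in Methods carry that sense by default. Fig. 1 and the full protocol were not available to settle it.

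Three stronger readings are tempting but not supported:

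- *Aim 3 selects on its own outcome.* It does not. Its endpoint is MES-rSO2, and NEC is a later event related to it.
- *The link from anemia to NEC can no longer be studied.* Statistical methods plans separate NEC analyses (cumulative incidence and cause-specific hazards), and the restriction is not attached to them.
- *The loss is large.* If anemia acts only through MES-rSO2, the loss is under a tenth in the scenarios worked here.

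The objections to the inputs also stand. The 5.99 is a hazard ratio for anemia in a given week, with a wide interval, while infants can change anemia status between weeks. SD 18 was stated for change around transfusion, not for weekly levels. The 20 cases are expected on study, not specifically within the window. These points limit the size that can be claimed. They do not remove the direction of the bias under the protocol's own hypothesis.

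**Conclusion.** The point holds on the plain reading. The Aim 3 set is conditioned on a later event that the protocol makes a consequence of both anemia and low MES-rSO2, and under that hypothesis the contrast is biased toward zero. For a true 10-point deficit, the worked range is from about 9.9 down to 6.4 points, depending mainly on how much anemia raises NEC risk other than through MES-rSO2. The strength of the MES-rSO2–NEC link, the anemic share and the SD for weekly levels are all assumed. If MES-rSO2 does not affect NEC, the bias is nil in this model, but that would contradict the study's premise.

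The article itself fixes this set, so it is a stated choice and not a detail left to an analysis plan. It should be fixed. It is not critical to the study: the aim is secondary and exploratory, and the Aim 1 primary endpoint is unaffected.

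**What to change.** In Methods, redefine the third sub-cohort as infants who are NEC-free on entering the 29–34 week window, chosen without regard to later NEC. Use each infant's weekly recordings up to NEC onset, death, discharge or the end of the window, whichever comes first. Report the never-NEC subset only as a sensitivity analysis. If NEC-free at each recording was always meant, one sentence saying so achieves the same.

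The cost is a change of wording and slightly unequal numbers of recordings per infant, which the analysis must allow for. No extra monitoring is needed for infants already recorded weekly. The change should be made before the 120 are chosen, because weekly recordings not taken in infants who go on to NEC cannot be recovered.

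When the sentence is edited, the anemia cut-off should also be reconciled: Aims includes a hemoglobin of exactly 8 g/dL and Methods does not.
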